### Multicentre trial and covariates

The specific trial design is a stratified multicentre trial with individual randomization at each involved centre. Using this design results in a gain in power [126], not a loss in power typical of randomized cluster trials where observations on individuals in the same cluster tend to be correlated. Therefore, no increase in the sample size is necessary even though we collect data at two research centres. In contrast, the sample size could be reduced for a given power [126]. Furthermore, in the statistical analysis (described below), we will adjust the analysis for the predictive covariates age, sex, VO_2_peak, and centre—the latter as appropriate when stratifying the randomization. Adjusting for covariates in the statistical analysis is also associated with a gain in statistical power, or equivalently, a reduced sample size requirement [127–129]. Yet, we have taken a conservative approach and have not accounted for this when estimating the required sample size due to the complex assumptions the calculations require, leading to uncertainty of how much reduction in the required sample size can be expected.

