## Methods: interventions

### Phase 1

Eligible participants will be randomized to perform either supramaximal HIIT (intervention arm) or MICT (active control arm) on a stationary bicycle (Smart ZBike, Zycle, Valencia, Spain) coupled to a tablet. For both arms, training is performed two to three times per week for a total of 30 sessions (Table 1) using a group format with groups of four to eight participants at the same time. Group training will be conducted in designated rooms at a training facility. Visual supporting information (additional file 4, Figure S4-S5) will be displayed on the tablet and will include the session elapsed time, elapsed time per programmed phase, revolutions per minute (RPM), and target power output (TPO).

**Table 1 Tab1:** Overview of exercise progression and progression criteria for supramaximal HIIT and MICT during phase 1

Block	Week	Session	HIIT % of MPO_6_	MICT % of MAP	General progression criteria		
	**0**	**Baseline testing**			**Criteria TPO escalation**	**HIIT**	**MICT**
**Mesocycle 1**: focus on intensity and duration (only MICT)	**1**	1	60%	50%	Able to maintain minimum RPM last interval/minute	80	60
		2	70%	55%	Exertion (RPE 6–20)	≤ 17	≤ 13
	**2**	3	80%	60%	Dyspnea (0–10)	≤ 7*	≤ 5
		4	#	¤	Note: Exertion and dyspnoea are assessed at the end of the last interval/minute		
	**3**	5	#	+ 2 min			
		6	#	¤			
	**4**	7	#	+ 2 min	**TPO progression criteria**		
		8	#	¤	**# Supramaximal HIIT % of workload**		
	**5**	9	#	+ 2 min	RPE ≤ 14 and dyspnoea ≤ 3	+ 5 to 10%	
		10	#	¤	RPE 15–17 and dyspnoea 4–7	+ 2.5 to 5%	
	**6**	11	#	+ 2 min	If RPE 18 or dyspnoea 8	Keep same	
		12	**CPET and BCST**		If RPE 19 or dyspnoea 9	-2.5 to -5%	
**Mesocycle 2**: increased frequency. Focus on increasing duration and intensity	**7**	13	#	¤	If RPE 20 or dyspnoea 10	-5 to -10%	
		14	#	¤	**¤ MICT % of workload**		
		15	#	¤	RPE ≤ 11 and dyspnoea ≤ 3	+ 5 to 10%	
	**8**	16	+ 1 interval	+ 2 min	RPE 12–13 and dyspnoea 4–5	+ 2.5 to 5%	
		17	#	¤	If RPE 14 or dyspnoea 6	Keep same	
		18	#	¤	RPE ≥ 15 or dyspnoea 7	-2.5 to -5%	
	**9**	19	+ 1 interval	+ 2 min	RPE ≥ 16 or dyspnoea ≥ 8	-5 to -10%	
		20	#	¤	Note: The highest rating informs the progression decision		
		21	#	¤			
	**10**	22	+ 1 interval	+ 2 min	**Duration progression criteria**		
		23	#	¤			
		24	#	¤	**Supramaximal HIIT duration**		
	**11**	25	+ 1 interval	+ 2 min	RPE ≤ 17 and dyspnoea ≤ 7	+ 1 interval	
		26	#	¤	If RPE 18 or dyspnoea 8	Keep same	
		27	#	¤	If RPE ≥ 19 or dyspnoea ≥ 9	- 1 interval	

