#### Outpatient

Participants with COPD that select to continue in an outpatient setting will perform HIIT and MICT training in the same manner as during the initial 12-week period, supervised in small groups of 4–8 participants (see Tables 2 and 3).

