### Sample size

Sample size calculations have been made to ensure that we have a sufficient sample size to detect difference in change in all three primary outcomes for both Phase 1 and 2. For these a priori power calculations, the sample size has been determined assuming a two-sided alpha level of 0.05 and 80% power.

### Phase 1

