#### Cognitive function

Assuming an SD of 0.4, a total sample size of 60 individuals (30 per group) is needed to detect a relevant difference of 0.27 in a global cognition z-score measured using a cognitive test battery [118]. A change in *z*-score of 0.27 is clinically relevant associated with increased all-cause, respiratory, and cardiovascular mortality. To account for a drop-out rate of approximately 15% at 3 months, a total of 70 participants is necessary.

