#### Muscle power and cardiorespiratory fitness

A sample size of 70 individuals (*n* = 35 per group) is also sufficient to detect a difference of 19.4% (SD 26.8%) [74] in quadriceps power (*n* = 30 per group) and to detect a relevant difference in maximal oxygen consumption (VO_2_max) of 3.5 mL/kg/min (SD 4.6 mL/kg/min) [119] (*n* = 26 per group) measured during a CPET. A difference of 3.5 mL/kg/min is associated with a 15% decrease in risk for cardiovascular disease [120]. No clinically relevant difference exists for muscle power; however, a difference of 19.4% is the minimal detectable change (MDC) from repeated testing of quadriceps peak power in older adults, as calculated by MDC = 1.96 × √2 × standard error of measurement (SEM) [74].

### Phase 2

In total, 138 individuals with COPD will be included in phase 2 (supramaximal HIT (*n* = 46), MICT (*n* = 46), and usual care (*n* = 46)). The sample size is estimated to account for an up to 30% additional drop-out rate at 24 months, in line with previous literature [121–123]. See phase 1 for complete details on the main sample size calculation. Additionally, as reported above in phase 1, the SD of 0.4 in the cognitive test battery is estimated from a trial in healthy adults comparing low to higher-intensity exercises [118] and not in patients with COPD. In phase 1, this uncertainty will be addressed with the increase in sample size from 70 to 92. However, for phase 2, we will instead perform an interim blinded sample re-estimation after half of the participants have performed baseline and 24-month follow-up, using recommended procedures for non-comparative data [124, 125], and adjust the sample size accordingly. These adaptations are recommended when there is any uncertainty in the SD. Importantly, using non-comparative data does not inflate the type I error probability or induce any bias in the treatment effect estimate (as it would if comparative data had been used) [124, 125].

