#### Statistical methods—outcomes

For primary and secondary outcomes with continuous data, treatment effect will be estimated by mean change-from-baseline (delta-value (Δ)) with 95% confidence intervals and the effect size (ES). The between-group effects will be analysed using analysis of covariance (ANCOVA). In the ANCOVA, baseline values, age, sex, centre, and VO_2_peak will be used as covariates. In phase 1, the primary analyses will be one model for the COPD group and one model for HC. In addition, to investigate any differential effects to the interventions between COPD and HC, a two-way ANCOVA including the Group (COPD/HC) × Intervention (supramaximal HIIT/MICT) interaction will be performed. In phase 2, there will be one model with the three arms (supramaximal HIIT, MICT, and usual care). Additional details will be provided in the SAP.

The assumptions of linearity, normality of residuals, and homogenous variance will be checked using residual plots, normal quantile plots, and histograms. Violations of linearity and normality assumptions will be dealt with by transformations of the dependent variable or non-linear modelling of the independent variables. Outliers will not be removed unless there is a methodological reason for it.

Feasibility of intervention outcomes and number of responders will be described with descriptive statistics and analysed with between group (HIIT/MICT) comparisons in both the COPD (phase 1 and 2) and HC group (phase 1).

In phase 1, hospitalization and exacerbations during the intervention will be presented descriptively. In phase 2, mortality, hospitalizations, and exacerbations will be presented with descriptive statistics and analysed using Kaplan–Meier curves and Cox proportional hazard models.

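### Phase 1 training is delivered in supervised groups, but the ANCOVA has no training-group term and the plan rules out a loss of power from correlated outcomes by considering centre only

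*Protocol article*

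**What the plan says.** - **Delivery.** Methods: interventions, Phase 1 has both arms training "using a group format with groups of four to eight participants at the same time". Table 3 gives 4 to 5 per group for the same period. Phase 1: supervision says that every session is supervised.
- **Analysis.** Statistical methods—outcomes: "In the ANCOVA, baseline values, age, sex, centre, and VO_2_peak will be used as covariates". Neither training group nor instructor appears. COPD and healthy controls have separate primary models in phase 1.
- **Sample size.** The calculations are made "assuming a two-sided alpha level of 0.05 and 80% power", with no design effect. For cognition, "a total sample size of 60 individuals (30 per group) is needed to detect a relevant difference of 0.27", with the SD stated as "Assuming an SD of 0.4".
- **Correlation.** Multicentre trial and covariates says that the stratified design gains power, "not a loss in power typical of randomized cluster trials where observations on individuals in the same cluster tend to be correlated", and concludes that two centres call for no increase in numbers.
- **Phase 2.** Outpatient training is "supervised in small groups of 4–8 participants" (Table 3 again says 4 to 5). Home training is individual and unsupervised. The mixed setting has one supervised session every two weeks.

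**The concern.** Stratifying by centre and adjusting for it removes between-centre variation from the HIIT versus MICT contrast. It does nothing about similarity that develops after randomisation among people who share sessions, an instructor and a social setting. A trial that randomises individuals but treats them in groups can have correlated outcomes even though allocation was individual.

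The article takes a position on correlated observations and concludes that no power is lost, using an argument that covers only one source of correlation. That is why the point stands although modelling detail is left to a separate SAP.

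At stake are the standard error of the phase 1 treatment contrast, hence the false-positive rate and interval width, and the power of a test that does hold its 5% level. There is also a practical risk: the adherence section documents attendance but names no group identifier, and membership may be hard to reconstruct later.

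**Working it through.** **Inputs from the article.** Two-sided alpha 0.05. Cognition: difference 0.27, SD 0.4. Quadriceps power: 19.4%, SD 26.8%. VO2: 3.5, SD 4.6 mL/kg/min. Dropout is about 15%, so COPD has 46 × 0.85 = 39 analysed per arm and healthy controls 35 × 0.85 = 30. Group size m is 4 to 8.

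**Assumptions.** ICC 0.01, 0.05 or 0.10 (the article gives none), with single-arm groups of fixed membership.

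**The plan's own figures, no clustering.** n per arm = 2 × (1.960 + 0.842)² × (SD/difference)² = 15.70 × (SD/difference)².
- Cognition: 15.70 × (0.4/0.27)² = 34.5, so 35 per arm against 30 stated.
- Quadriceps power: 15.70 × (26.8/19.4)² = 30.0, so 30, as stated.
- VO2: 15.70 × (4.6/3.5)² = 27.1, so 28 against 26 stated.

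The cognition shortfall is a separate matter that clustering does not explain. The baseline below is therefore the power under independence, not the nominal 80%.

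**Formulae.** Design effect DE = 1 + (m − 1) × ICC. Intervals should be √DE times as wide. False-positive rate of the unadjusted test = 2 × [1 − Φ(1.96/√DE)]. Power comes from the noncentral t distribution with noncentrality (difference/SD) / √(2 × DE/n) and 2n − 2 degrees of freedom.

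Example: cognition, n = 39. Under independence the noncentrality is 0.675/√(2/39) = 2.98 and power is 83.7%. With m = 6 and ICC 0.05, DE = 1.25, the noncentrality is 2.98/1.118 = 2.67 and power is 74.9%.

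| ICC | m | DE | √DE | False positive, formula | False positive, simulated | Cognition power, n = 39 |
|---|---|---|---|---|---|---|
| 0.01 | 4 | 1.03 | 1.015 | 5.3% | 5.4% | 82.6% |
| 0.01 | 8 | 1.07 | 1.034 | 5.8% | 5.6% | 81.2% |
| 0.05 | 4 | 1.15 | 1.072 | 6.8% | 6.6% | 78.4% |
| 0.05 | 6 | 1.25 | 1.118 | 8.0% | 7.7% | 74.9% |
| 0.05 | 8 | 1.35 | 1.162 | 9.2% | 9.0% | 71.7% |
| 0.10 | 4 | 1.30 | 1.140 | 8.6% | 8.5% | 73.3% |
| 0.10 | 8 | 1.70 | 1.304 | 13.3% | 13.1% | 61.7% |

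The simulation drew 40,000 two-arm trials per setting, with random group intercepts and a t-test that ignores groups.

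**Other outcomes, COPD, m = 6, ICC 0.05.** Quadriceps power falls from 88.4% to 80.6%, VO2 from 91.3% to 84.3%.

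**Healthy controls, n = 30, m = 6, ICC 0.05.** Cognition falls from 72.9% to 63.3%, quadriceps power from 78.7% to 69.4%, VO2 from 82.6% to 73.6%.

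**Break-even for COPD cognition.** The t-based requirement is 35.4 per arm, so 80% power holds up to DE = 39/35.4 = 1.10. That is an ICC of 0.10/3 = 0.033 at m = 4, or 0.10/7 = 0.014 at m = 8.

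**Mixed-arm groups.** With each group split equally between the arms and 39 per arm, the unadjusted test rejected in 3.9% to 5.0% of 20,000 null trials per setting, which is slightly conservative.

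**The case against.** - **It is conditional.** The article gives no ICC and does not say that groups are arm-specific, stable, or separate for COPD and healthy controls. A reader might infer that the intervals are too narrow; the article does not establish that. Separate groups are implied by session length (20 against 30 minutes), cadence (80–90 against 60–70 RPM) and an instructor cue that fits only HIIT. This limits the size of the problem; it does not remove the gap.
- **Dose is individual.** Load progresses on each person's own ratings and tests, instructor overrides are meant for individuals and must be documented, encouragement is kept modest, and assessors are masked. This stands, and favours the low end of the ICC range.
- **Clusters may be small or shifting.** Trial status reports 51 enrolled in about ten months, which suggests rolling membership, and COPD and healthy controls are modelled separately. That would shrink the effective m, so the m = 8 rows are extremes.
- **There is slack.** Covariate adjustment was deliberately left out of the sizing and may recover power, though it does not repair the false-positive rate. COPD enrolment rises from 70 to 92, but the article assigns that to uncertainty in the SD, and healthy controls have no such increase.
- **The SAP may deal with it.** It may add a group term. The correlation statement in the article would still cover centre only.

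**Conclusion.** The point holds in conditional form and mainly for phase 1. The article rules out a loss of power from correlated observations by reasoning about centre, while both arms are trained in supervised groups that the listed model omits. With a positive ICC and single-arm groups, the unadjusted intervals should be 1.5% to 30% wider over the assumed range. The false-positive rate is about 5.4% to 13%, and COPD cognition power is about 83% to 62% against 83.7% under independence. At ICC 0.01 the cost is only 1 to 3 points of power.

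Two stronger readings are not supported. One is that power should be restated at a single lower value, such as the 74.9% at ICC 0.05 and m = 6; with no ICC in the article, only a range can be defended. The other is that phase 2 requires a partially nested model. Participants choose and may switch settings, and only outpatient training is fully grouped, so the concern there applies mainly to that subset and such a model is optional.

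**What to change.** 1. State how training groups are formed, and record a training-group and an instructor identifier for every phase 1 participant.
2. Add a random intercept for training group to the phase 1 ANCOVA models, with Satterthwaite or Kenward-Roger degrees of freedom, or at minimum pre-specify this as a sensitivity analysis. Report the ICC.
3. In Multicentre trial and covariates, limit the statement about power to centre, and show power over a range of ICC values for COPD and for healthy controls.
4. Reconcile the group size in the text (4 to 8) with Table 3 (4 to 5).

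**Cost.** Two identifier fields in the eCRF, a modest change of model, and SAP wording. The downside is fewer degrees of freedom, with about 5 to 10 groups per arm (39/8 to 39/4), and a less favourable stated power. If group variance is near zero, the results should barely change. No extra enrolment is needed.

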### Allocation, randomization, and masking

In phase 1, participants will be randomized to either interventional arm or control arm with a 1:1 allocation ratio, using a computer-generated (Sealed Envelope Ltd., London, UK) blocked randomization schedule with varying block sizes of two or four, stratified by sex (male, female) and centre with equal allocation to all trial arms. For phase 2, only the participants with COPD will continue the maintenance program in their allocated group.

Group allocation will be performed after participants have been recruited into the trial; baseline assessments have been completed and eligibility confirmed. The allocation sequence will be kept in an opaque, tamper-proof sealed, and stapled envelope that will be concealed until the end of the outcome assessment. By using aluminium foil inside the envelope, it will be impermeable to intense light. A delegated person independent from enrolment, assessments, and training will generate the allocation sequence, enrol participants, and assign participants to interventions.

Outcome assessors and data analysts will be masked to group allocation. Participants will be instructed not to reveal their group allocation to the outcome assessor during interim-, 12-week, and 24-month trial assessments. In case of failure of keeping the outcome assessor masked, a second outcome assessor will be available. Given the nature of the interventions, neither participants nor instructors of the training sessions can be masked during the intervention. Hypotheses of the trial will not be revealed to the participants during their participation.

### Data management

The REDCap (Research Electronic Data Capture) Survey, a secure, Health Insurance Portability and Accountability Act compliant, web-based survey application will be used as an eCRF. The eCRF system has been set up by the ICT Services and System Development at Umeå University. The data is stored at local servers and is backed up daily. In the eCRF, quality control checks, such as validation of data type and expected data range, is used. Notifications and prompts are used if data is missing, outside of expected range or indicate participant eligibility. The majority of trial data is directly entered into the eCRF during and after trial visits, using a computer or tablet. Some data, such as ratings of exertion during exercise, will be collected on paper CRFs and later entered into the eCRF.

Other electronic data will also be generated outside of REDCap. This includes data files generated by metabolic carts (CPET, BCST, CWRT), lung function assessments, and blood and muscle sample data. These data will be stored on local databases designated for research data.

All data will be pseudonymized. Consenting participants will be assigned a unique sequential participant identification code. While this ID will be linked to personal data, only the ID code will be used during data collection and analysis to protect participants’ integrity. The participants’ identities will only be known by the research group at the respective centre and the PI. It will not be possible to identify specific individuals in the trial.

All hard-copy records with participant information, such as informed consent forms, will be stored separately in locked file cabinets in areas with limited access and separate from trial records identified by ID code at the local research centres, respectively. All personal data will be processed in accordance with the EU General Data Protection Regulation (GDPR).

### Statistical methods

The change-from-baseline analyses will be performed after the last participant has completed all assessments of phase 1 and phase 2, respectively, after monitoring and data quality checks. Analyses will be performed blinded by the investigators supported by a biostatistician. All statistical tests will be conducted as two-sided, with the alpha level set at 0.05.

Baseline variables and descriptive statistics with continuous data will be presented with mean (SD) or median (IQR) as appropriate. Continuous data with normative values (for example, VO_2_peak and lung function values) will also be presented as % predicted value. Ordinal variables will be presented as median (IQR) or as *n* (%), and categorical variables will be presented as *n* (%).

A separate detailed SAP with further details about the statistical analyses including the method to handle family-wise error rate for the multiple primary outcomes will be published and finalized before the database is locked and randomization codes unblinded. In line with recommendations, it increases transparency and replicability and might be updated in response to new methods, challenges encountered during the trial, funding availabilities, and emerging evidence during the period of the trial [130, 131].

#### Statistical methods—outcomes

For primary and secondary outcomes with continuous data, treatment effect will be estimated by mean change-from-baseline (delta-value (Δ)) with 95% confidence intervals and the effect size (ES). The between-group effects will be analysed using analysis of covariance (ANCOVA). In the ANCOVA, baseline values, age, sex, centre, and VO_2_peak will be used as covariates. In phase 1, the primary analyses will be one model for the COPD group and one model for HC. In addition, to investigate any differential effects to the interventions between COPD and HC, a two-way ANCOVA including the Group (COPD/HC) × Intervention (supramaximal HIIT/MICT) interaction will be performed. In phase 2, there will be one model with the three arms (supramaximal HIIT, MICT, and usual care). Additional details will be provided in the SAP.

The assumptions of linearity, normality of residuals, and homogenous variance will be checked using residual plots, normal quantile plots, and histograms. Violations of linearity and normality assumptions will be dealt with by transformations of the dependent variable or non-linear modelling of the independent variables. Outliers will not be removed unless there is a methodological reason for it.

Feasibility of intervention outcomes and number of responders will be described with descriptive statistics and analysed with between group (HIIT/MICT) comparisons in both the COPD (phase 1 and 2) and HC group (phase 1).

In phase 1, hospitalization and exacerbations during the intervention will be presented descriptively. In phase 2, mortality, hospitalizations, and exacerbations will be presented with descriptive statistics and analysed using Kaplan–Meier curves and Cox proportional hazard models.

In phase 2, pre-specified longitudinal mediation analyses will be performed on the entire MRI and PET/CT sample between changes in VO_2_peak, neurodegenerative measures, such as cognitive function and hippocampal volume and inflammation levels between baseline and 24 months. In these models, we will determine how inflammation mediates the effect of exercise training on neurodegenerative measures, including global cognitive function, hippocampal volume, and grey matter in the posterior, anterior, and midcingulate cingulate cortex, respectively, using a set of linear regression and maximum likelihood estimations [132]. Additionally, we will test whether the exercise training intensity (supramaximal HIT vs. MICT) has a different mediating effect. Additional details will be provided in the SAP.

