### Trial design

COPD-HIIT is a prospective, multi-centre, randomized, controlled, parallel-group superiority trial with the assessor and statistician blinding, featuring a 1:1 allocation ratio and two separate phases. In phase 1, we will investigate the effects and mechanisms of a 12-week intervention with supramaximal HIIT compared to MICT in people with COPD and matched healthy controls. Upon completion of the initial 12-week intervention and follow-up assessments, people with COPD, but not healthy controls, will enter phase 2 of the trial. Phase 2 comprises a 21-month maintenance exercise program. Subsequently, exercise training (supramaximal HIIT or MICT) will be performed until a 24-month follow-up. A separate control group of people with COPD, receiving usual care only, will undergo assessments at baseline and 24 months. As the usual care arm is not included in the randomization, phase 2 is a partially randomized controlled trial. See Fig. 1 and Fig. 2 for an overview of the COPD-HIIT project design.

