#### Resistance training (RT)

Irrespective of the originally assigned group (supramaximal HIIT or MICT) and chosen setting, all participants will also perform a RT regime. The RT regime will consist of ten lower- and upper-body exercises designed following American College of Sports Medicine guidelines [49] and other relevant RT literature for increasing muscular strength, endurance, and power. The goal of the RT regime (strength, endurance, or power) will change monthly. See Table 4 and additional file 5, Figure S1-S3 for details of the RT regime.

**Table 4 Tab4:** Description of resistance training (RT) in line with TIDieR and CERT guidelines

Variable	Description
1. RT objective	The aims of the RT exercises are to improve limb muscle strength, power, and endurance
2. Training device and type of exercise	All exercises will be performed using the body weight of the participant and/or with elastic bands (Thera-Bands®, The Hygienic Corporation, Akron, OH, USA). The participants will be provided with the elastic bands. If performed in an outpatient setting, available RT equipment will be used. (Umeå: leg press, leg extension, chest press and lat pull-down machines, Nautilus, Core Health and Fitness LLC, Vancouver, WA, USA. Hasselt: lat pull-down and leg press machines, Enraf–Nonius B.V. Echt, The Netherlands). At both centres, Free-weight dumbbells, (Ziva, Raleigh, NC 27606, USA) will be used for elbow and shoulder flexion)
3. Provider & Location	Each session will be performed unsupervised in the home setting of the participant or in an outpatient setting (local gym or rehab centre) or in an outpatient setting (local gym or rehab centre). The RT is performed individually and delivered via a two-weekly phone call
4. Warm-up	No specific warm-up will be conducted before start of the RT
5. Muscle actions	Exercises will be performed using dynamic concentric/eccentric muscle actions

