#### Passive control group: usual care

The passive control group will receive usual care alone and a standardized phone call (see additional file 4) every 3 months including assessment of symptoms of exacerbations. Health status (CAT) and disease-specific quality of life (CRQ) will be assessed by sending a letter with the questionnaires via the post for self-administration or by a phone call. We will match the participants in the usual care group to those randomized to HIIT or MICT by age, sex, disease severity (GOLD A/B/E), educational level, and physical activity.

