#### Statistical methods—additional analyses

Pairwise comparisons between COPD and healthy controls will be conducted at baseline to investigate if matching has been successful, as well as to compare the cohorts using recommended methods for parametric and non-parametric data.

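### The Phase 2 model omits three of the five factors used to match the non-randomised usual-care arm, so contrasts with usual care may carry residual confounding

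*Protocol article*

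**What the plan says.** All references are to the protocol article.

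- **Allocation.** Trial design states: "As the usual care arm is not included in the randomization, phase 2 is a partially randomized controlled trial".
- **Matching.** The section on the passive control group matches usual-care participants to those randomised to HIIT or MICT "by age, sex, disease severity (GOLD A/B/E), educational level, and physical activity". It gives no matching ratio or tolerance.
- **Model.** Statistical methods—outcomes specifies the adjustment: "In the ANCOVA, baseline values, age, sex, centre, and VO_2_peak will be used as covariates". It puts all three arms into a single Phase 2 model. The section on multicentre design and covariates gives the same list, apart from the baseline value: "we will adjust the analysis for the predictive covariates age, sex, VO_2_peak, and centre". There the reasons are power and the stratification of the randomisation by centre.
- **Deferral.** After describing the three-arm model, the article adds: "Additional details will be provided in the SAP".
- **Check of matching.** The only one described concerns the other matched comparison: "Pairwise comparisons between COPD and healthy controls will be conducted at baseline to investigate if matching has been successful".
- **Content of the arms.** In the maintenance phase, whether assigned to HIIT or MICT, "all participants will also perform a RT regime". Table 4 gives limb muscle power among the aims of that training. Exercise arms are phoned every 14 days, usual care every 3 months.

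**The concern.** In a randomised contrast, covariates mainly buy precision, and choosing them for predictive value is sound. In a contrast with a non-randomised arm they also have to control confounding. The plan carries a list justified by the first purpose over to the second. It names five factors as important enough to match on, then adjusts for only two of them.

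The second primary objective rests partly on these contrasts, because it compares 24 months of HIIT, MICT and usual care on cognitive function, cardiorespiratory fitness and quadriceps power. If the arms still differ in severity, education or activity after matching, part of an apparent exercise effect could be that difference.

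A related, secondary point concerns what the contrast estimates. Resistance training and fortnightly contact go only to the exercise arms. A difference from usual care therefore belongs to the whole package. This matters most for quadriceps power, which the resistance training is itself meant to improve.

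**Working it through.** **Step 1: compare the lists.**

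| Matching factor | In the ANCOVA? |
|---|---|
| Age | Yes |
| Sex | Yes |
| GOLD A/B/E | No |
| Educational level | No |
| Physical activity | No |

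Three of five are missing. The model also holds the baseline value of the outcome, centre and VO2peak, which are not matching factors. No term for the matched sets is stated.

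**Step 2: inputs for size.** The protocol gives an SD of 0.4 and a target difference of 0.27 for the cognitive z-score, 46 per arm, and up to 30% additional drop-out, which leaves 46 × 0.70 = 32.2, about 32 per arm. It gives neither the imbalance left after matching nor the correlation of the omitted factors with change. Both are assumptions here and should be read as what remains after the covariates already in the model.

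**Step 3: bias per omitted factor.** Bias ≈ imbalance (SD units) × partial correlation with change × SD of change.

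- No imbalance: 0 × correlation × 0.4 = 0.
- Low end: 0.2 × 0.2 × 0.4 = 0.016; 0.016 / 0.27 = 6%.
- High end: 0.5 × 0.3 × 0.4 = 0.06; 0.06 / 0.27 = 22%.

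**Step 4: three factors together.** If all three run in the same direction, the biases add. The standard error of a two-arm difference at 32 per arm is 0.4 × √(2/32) = 0.10. A 4000-run linear-model simulation, at partial correlation 0.2 for each factor and with no true effect, gave:

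| Imbalance on each | Bias by formula | Share of 0.27 | Simulated bias, omitted | Type I error, omitted | Type I error, included |
|---|---|---|---|---|---|
| 0 (exact matching) | 0 | 0% | −0.001 | 0.038 | 0.048 |
| 0.25 SD | 3 × 0.25 × 0.2 × 0.4 = 0.06 | 22% | 0.064 | 0.095 | 0.055 |
| 0.5 SD | 3 × 0.5 × 0.2 × 0.4 = 0.12 | 44% | 0.121 | 0.229 | 0.050 |

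With the three factors in the model, the simulated bias was within 0.002 of zero in every row. Over a wider grid (imbalance 0.1–0.5 SD, correlation 0.1–0.3), the three-factor bias runs from 3 × 0.1 × 0.1 × 0.4 = 0.012 to 3 × 0.5 × 0.3 × 0.4 = 0.18.

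**Step 5: contrasts affected.** HIIT and MICT are randomised against each other, so omitting these factors does not confound that contrast. Only HIIT versus usual care and MICT versus usual care are exposed.

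**The case against.** Matching is itself a control for the omitted factors. If it balances them, leaving them out of a linear model produces no bias and only a slightly conservative test (0.038 in the simulation). This stands, and it rules out saying that confounding is known to remain: the protocol reports no imbalance.

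Baseline outcome and VO2peak may absorb part of any difference in severity or activity, and the outcome is change rather than level. This also stands. It means that plausible values may lie towards the lower end of the ranges.

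A reader might infer that drop-out differs between arms. The documents give only an overall allowance. They also plan intention-to-treat analysis where applicable, multiple imputation by arm, and sensitivity analyses for data not missing at random. Erosion of the matching by drop-out is therefore a possibility, most direct in the complete-case and per-protocol analyses. It can also reach the imputed analysis if the imputation model lacks these factors.

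Further model detail is left to the SAP, which is not shown and may add covariates. A balance table for usual care against the exercise arms is ordinary SAP content, so its absence here is no fault. The covariate list is different: it is stated in two places and applied to the three-arm model.

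Finally, the protocol openly describes the resistance training and the calls, and it labels Phase 2 as partially randomised. That is fair, but the objective still words the comparison as one of HIIT, MICT and usual care.

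**Conclusion.** The point holds as a risk. The stated Phase 2 covariates omit GOLD group, educational level and physical activity, although the usual-care arm is matched on them. Residual confounding may remain in HIIT or MICT versus usual care if matching is loose or is eroded by drop-out.

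The size cannot be derived from the documents. It is zero under balance and about 0.016–0.06 z per factor under the assumed imbalance of 0.2–0.5 SD, partial correlation of 0.2–0.3 and SD 0.4. It is larger if several factors are out of balance in the same direction.

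The stronger readings, that the usual-care estimate is certainly biased or that the comparison of the two exercise arms is compromised, are not supported. The change is worth making because it is cheap and protects the contrasts that randomisation does not.

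**What to change.** 1. In the SAP, for the Phase 2 contrasts with usual care, add GOLD group (A/B/E), educational level and baseline physical activity to the ANCOVA covariates already listed.
2. Put the same three variables into the imputation model used for that analysis.
3. Keep HIIT versus MICT as the randomised contrast, and present the usual-care contrasts separately, labelled as non-randomised.
4. Word the usual-care contrasts as estimates of the whole exercise package (endurance training, resistance training and more frequent contact), not of HIIT or MICT alone, and say so explicitly for quadriceps power.

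It would also help to tabulate standardised differences between usual care and the exercise arms, at baseline and among those assessed at 24 months.

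Cost: SAP text, settled before database lock. No new data are needed: education and physical activity are among the baseline assessments, and GOLD group must be known in order to match on it. The model loses about 4–5 degrees of freedom. Because imputation is run within each arm of 46, the extra terms weigh somewhat more there, so education is best kept to a few categories.
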